## 474 6.5 Efficacy Assessments

475 Screening assessments must include magnetic resonance imaging (MRI) with gadoxetate  
476 disodium as well as dual-tracer PET-CT with contrast enhanced triphasic CT scan of the liver  
477 for tumor contouring and treatment planning for SBRT.

478 Follow-up imaging with MRI with gadoxetate disodium injection and dual-tracer PET-CT  
479 scan with contrast-enhanced triphasic CT scans every 3 months after SBRT will be arranged  
480 for treatment response evaluation by RECIST 1.1, mRECIST, and PERCIST  
481 (APPENDIX 4 and APPENDIX 5) and surveillance for recurrence/relapse.

482 At the investigator's discretion, scans should be repeated at any time if progressive disease is  
483 suspected.

484 Confirmation of progression guidelines are set for the following reasons:

- 485 • for patient management and treatment decisions
- 486 • when scans are evaluated by two independent radiologists.

Confirmed objective disease progression refers to either of the following scenarios: 1. clinical progression/deterioration followed by a radiologic verification scan (progressive disease [PD] by RECIST 1.1, mRECIST, and PERCIST); or 2. in the absence of significant clinical deterioration, radiologic PD by RECIST 1.1, mRECIST, and PERCIST followed by a second radiologic confirmation scan with PD assessed according to the specific confirmation of progression criteria listed below. The confirmatory scan should occur preferably at the next scheduled imaging visit and no earlier than 4 weeks following the date of the immediate prior assessment of PD.

Immediate prior radiologic progression would be considered confirmed if any the following criteria are met in the confirmatory scan:

- $\geq 20\%$  increase in the sum diameters of target lesions (TLs) compared with the nadir at 2 consecutive visits, with an absolute increase of at least 5 mm in sum of diameters compared to nadir,

- and/or significant progression (worsening) of non-target lesions (NTLs) and/or of pre-existing new lesions at the confirmatory scan time-point compared with the immediate prior time-point (Note: Pre-existing new lesions are evaluated as NTLs at the confirmatory scan time-point),

- and/or additional new unequivocal lesions at the confirmatory scan time-point.

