|  | 
uptake (75% in TLA/TLG volume with no decline in SUL. OR: New ACC and/or FDG-avid lesions that are typical of cancer and not related to treatment effect or infection. PMD other than new visceral lesions should be confirmed on follow-up study within 1 month unless PMD also is clearly associated with progressive disease by RECIST 1.1. PMD should be reported to include percentage change in SUV peak, (ideally, time after treatment, in weeks) and whether new lesions are present/absent and their number (i.e., PMD, +35, 4, new: 5). Because SUL is continuous variable, dividing response criteria into limited number of somewhat arbitrary response categories loses much data. For this reason, PERCIST preserves percentage declines in SUV peak in each reported category. Because rapidity with which scan normalizes is important (faster appears better), PERCIST asks for time from start of treatment as part of reporting. For example, CMR 90, 1, is probably superior to CMR 90, 10, especially if latter patient were SMD20, 1. More than one measurement of PET response may be needed at differing times, and it may be treatment type-dependent. PERCIST 1.0 evaluates SUL peak of only hottest tumor. This is possible limitation of approach, but lesions and their responses are highly correlated in general. Additional data are required to determine how many lesions should be assessed over 1. A suggested option is to include the 5 hottest lesions, or the 5 observed on RECIST 1.1 that are most measurable. Percentage change in SUL can be reported for single lesion with largest increase in uptake or smallest decline in uptake. Additional studies will be needed to define how many lesions are optimal for assessment.
 |

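### Section 6.5 does not accept a new tumour that merely persists as confirmation of progression, so a patient with no other finding is not a PFS event there, while Appendix 5 counts an avid one at once

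*Protocol*

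**What the plan says.** Protocol Sections 2.1 and 8.1.1 and the synopsis define PFS from the start of SBRT to radiologically confirmed progression by RECIST 1.1, mRECIST and PERCIST, or death. Section 8.1.1 does not say what makes progression confirmed. Section 6.5 does, and gives two routes.

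- The first is "clinical progression/deterioration followed by a radiologic verification scan".
- The second, for patients without significant clinical deterioration, is progression on one scan followed by a second scan, "no earlier than 4 weeks following the date of the immediate prior assessment of PD" and preferably at the next scheduled visit.

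On the second route the confirmatory scan must meet at least one of three criteria:

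- at least a 20% "increase in the sum diameters of target lesions (TLs) compared with the nadir at 2 consecutive visits", with an absolute rise of at least 5 mm;
- significant worsening of non-target lesions, or "of pre-existing new lesions at the confirmatory scan time-point compared with the immediate prior time-point", with the note that "Pre-existing new lesions are evaluated as NTLs at the confirmatory scan time-point";
- "additional new unequivocal lesions at the confirmatory scan time-point".

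If none is met, Section 6.5 says the patient continues until the next progression, which again needs a confirmation scan. The investigator's reading of the first scan is left as recorded.

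Appendix 5 (PERCIST) makes a new FDG- or acetate-avid lesion typical of cancer progressive metabolic disease (PMD). Its confirmation rule reads: "PMD other than new visceral lesions should be confirmed on follow-up study within 1 month", unless RECIST 1.1 progression is clearly present as well.

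**The concern.** When the first progression is a new lesion, the natural confirmation is that the lesion is still there on the next scan. Section 6.5 asks for more: the lesion must have worsened again, or something else must have progressed. A new liver tumour that persists at about the same size satisfies nothing on the list.

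PFS is a co-primary endpoint in the synopsis, and Section 8 calls it the primary endpoint. If real new tumours are left unconfirmed, some PFS events come late or are not counted, and the error runs in one direction, towards longer PFS. In addition, two analysts could classify the same patient differently, one following Section 6.5 and the other Appendix 5.

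**Working it through.** No plan figure is at issue, so the check is to run one patient through each passage.

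**Test patient.** SBRT controls the target lesions. Scan 1 shows one new avid HCC in the liver. On scan 2 it is still present and not significantly worse. There is no other change and no clinical deterioration.

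**Section 6.5**

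1. Clinical route: not available, because there is no deterioration.
2. Target-lesion growth: not met; the target lesions are controlled.
3. Worsening of non-target or already-seen new lesions: not met. The new lesion is now judged as a non-target lesion against scan 1, and it has not significantly worsened.
4. Additional new lesions: not met; the only new lesion is the one already seen.

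Result: progression is not confirmed and the patient continues.

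**Appendix 5.** A new avid lesion typical of cancer is PMD at scan 1. A liver lesion is visceral, so the confirmation requirement does not apply. Result: progression at scan 1.

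Section 6.5 names PERCIST among the criteria to which its confirmation rule applies. The two results therefore cannot be put down to each passage governing a different criterion.

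**Effect on the event date, as a constructed illustration.** Take Section 6.5's 3-monthly scans and its preference for confirming at the next scheduled visit. Suppose the lesion appears at month 3, is unchanged at month 6, is significantly worse at month 9 and worse again at month 12.

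- Appendix 5 gives an event at month 3.
- Section 6.5 does not confirm at month 6, takes month 9 as the next progression and confirms it at month 12.
- Dated at the next progression, the event is 9 − 3 = 6 months later; dated at its confirmation, 12 − 3 = 9 months later. Section 6.5 does not say which scan supplies the date.
- Study imaging runs until transplantation or progression (synopsis; Appendices 2 and 3). If the patient is transplanted at, say, month 8, the worsening is never observed and the lesion may never become an event.

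This shows the mechanism for one patient. It cannot be scaled to the trial, because the documents do not say how often a new lesion is the only finding or how often it stays stable.

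**Related mismatches**

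- For PMD that does need confirmation, Appendix 5 wants the follow-up within 1 month, whereas Section 6.5 allows it no earlier than 4 weeks (28 days). Only about 31 − 28 = 3 days at most satisfy both, and the preferred 3-monthly visit does not.
- The Appendix 4 tables define progression by sums of target-lesion diameters and list no new-lesion criterion, although Section 6.5 assumes that new lesions count.

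**The case against.** The strongest reply is that Section 6.5 is not an endpoint definition. The first purpose it gives for its confirmation rules is patient management and treatment decisions, and Section 8.1.1 does not refer to it. On that view, radiologically confirmed could mean no more than shown on imaging. This has some force and is why the wording needs settling. But the PFS definition uses the term confirmed, no other passage gives it a general meaning, and Section 6.5 follows patients until confirmed objective progression. Its rule is the natural one to apply.

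Other routes to confirmation exist: target-lesion growth, worsening of other non-target lesions, an additional lesion, or clinical deterioration with a verification scan. A reader might infer that any new tumour must itself grow before it counts; the text does not say that. Only the patient with no other finding is caught.

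A reader might also infer that such events are permanently lost. Assessment continues to the next progression, and the first reading is kept, so many could be recovered. Keeping that reading does not, however, make it confirmed.

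It is tempting to apply the 20% and 5 mm limits to a new lesion and calculate how slowly it must grow to escape confirmation. The documents do not support this: those limits apply to the sum of target-lesion diameters, while new lesions are judged by significant worsening with no number attached.

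Finally, different response criteria may legitimately disagree about a lesion, and Appendix 5 covers only avid ones. That limits the contradiction to new avid visceral lesions; a non-avid new HCC falls outside it. Within that limit the contradiction stands, because Section 6.5 applies its own rule to PERCIST.

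**Conclusion.** The point holds in this form: a persistent new lesion that is the only finding, without clinical deterioration and without significant worsening, is unconfirmed under Section 6.5; if it is avid and visceral, it is progression without confirmation under Appendix 5. The direction of the bias is clear, since PFS can only be lengthened. Its size cannot be derived from the documents, and any percentage of events lost would be a guess.

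The conclusion rests on two readings: that confirmed in the PFS definition has the meaning given in Section 6.5, and that progression is assessed under each response criterion in turn.

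This should be fixed before analysis, but it does not undermine the stated design. The 28 patients are justified by objective response (60% against 85%), and no null or target value for PFS is given, so no stated decision rule changes. What is at risk is the PFS estimate and whether it can be reproduced.

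**What to change.** Reconcile Sections 6.5 and 8.1.1 with Appendices 4 and 5 on whether and how a new lesion becomes a PFS event. In the PFS endpoint definition, and for analysis only, state that:

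- a new unequivocal lesion still present on the confirmatory scan counts as confirmed progression, whether or not it has grown;
- additional new lesions remain a further sufficient criterion;
- a named scan, the one first showing progression or the confirming one, supplies the event date.

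Add the new-lesion criterion to Appendix 4 or refer to where it is defined, and align the confirmation timing in Appendix 5 with Section 6.5.

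Confirmed progression is also a ground for permanent treatment discontinuation in Section 5.2, and Section 6.5 ties the same rules to treatment decisions. The endpoint wording should not alter those uses; the sponsor must reconcile them separately.

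The cost is a wording change. It needs no extra scans or patients. Estimated PFS may come out slightly shorter.

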## **6.6 Physical Examination**

A complete physical examination should be performed at baseline, during SBRT until 3 months after SBRT, including height and weight measurements, and examinations of the respiratory system, abdomen and central nervous system. At subsequent visits, limited, symptom-directed physical examinations should be performed. Changes from baseline abnormalities should be recorded in patient notes.

525 Performance status will be assessed using ECOG performance status at each visit based on  
526 the following:

0 Fully active, able to carry on all pre-disease performance without restriction

1 Restricted in physically strenuous activity but ambulatory and able to carry out work of a light or sedentary nature, e.g., light house work, office work

2 Ambulatory and capable of all selfcare but unable to carry out any work activities; up and about more than 50% of waking hours

3 Capable of only limited selfcare; confined to bed or chair more than 50% of waking hours

4 Completely disabled; cannot carry on any selfcare; totally confined to bed or chair

5 Dead

## 527 **6.7 Clinical Safety Laboratory Assessments**

528 All recruited patients shall undergo baseline screening investigations including blood tests  
529 for serum hematology, biochemistry, clotting profile, alfa-feto protein and hepatitis B and C  
530 serology. All patients will be monitored once weekly during SBRT for any side effects, then  
531 monthly for 3 months followed by every 2-3 months with the aforementioned blood tests for  
532 serum hematology, biochemistry and clotting profile, alfa-feto protein and hepatitis B and C  
533 serology. The laboratory variables to be measured are presented in the following tables:

### **Hematology**

|                      |             |
|----------------------|-------------|
| Platelet Count       | Basophils   |
| Red Blood Cell Count | Eosinophils |
| Hemoglobin           | Lymphocytes |
| Hematocrit           | Monocytes   |
|                      | Neutrophils |

### **Clinical biochemistry (serum)**

|                                 |                             |
|---------------------------------|-----------------------------|
| Albumin                         | Glucose                     |
| Alkaline phosphatase            | Lactate dehydrogenase (LDH) |
| Alanine aminotransferase        | Potassium                   |
| Aspartate aminotransferase      | Sodium                      |
| Calcium                         | Total bilirubin             |
| Chloride                        | Total bilirubin             |
| Creatinine                      | Total protein               |
| Gamma glutamyltransferase (GGT) | Urea                        |
| Globulin                        |                             |

Tests for ALT, AST, alkaline phosphatase, and total bilirubin must be conducted and assessed concurrently. If total bilirubin is  $\geq 2 \times$  upper limit of normal (and no evidence of Gilbert's syndrome) then fractionate into direct and indirect bilirubin.

b Bicarbonate (where available), chloride, creatinine clearance, gamma glutamyltransferase, and magnesium testing are to be performed at baseline, on Day 0 (unless all screening laboratory clinical chemistry assessments are performed within 3 days prior to Day 0), and if clinically indicated.

c Creatinine Clearance will be calculated by data management using Cockcroft-Gault (using actual body weight).

### Clotting profile

|     |                                                           |
|-----|-----------------------------------------------------------|
| INR | Prothrombin time
Activated partial thromboplastin time |
|-----|-----------------------------------------------------------|

### Hepatitis B and C serology

|                          |                                                         |
|--------------------------|---------------------------------------------------------|
| HBsAg
HBeAg, Anti-HBc | Anti-HBs
for hepatitis B
Anti-HCV for hepatitis C |
|--------------------------|---------------------------------------------------------|

534 Those patients who are found to be current or past hepatitis B or C carriers must receive  
535 adequate anti-viral therapy as per local institution's routine clinical practice.

536 All patients with Grade 3 or 4 laboratory values at the time of completion or discontinuation  
537 from this study must have further tests performed until the laboratory values have returned to  
538 Grade 1 or 2, unless these values are not likely to improve because of the underlying disease.

## 539 6.8 Safety Reporting

### 540 6.8.1 Adverse Events (AE)

541 The International Conference on Harmonization (ICH) Guideline for Good Clinical Practice  
542 (GCP) E6(R1) defines an AE as:

543 Any untoward medical occurrence in a patient or clinical investigation patient administered a  
544 pharmaceutical product and which does not necessarily have a causal relationship with this  
545 treatment. An AE can therefore be any unfavorable and unintended sign (including an  
546 abnormal laboratory finding), symptom, or disease temporally associated with the use of a  
547 medicinal product, whether or not considered related to the medicinal product.

548 An AE includes but is not limited to any clinically significant worsening of a patient's pre-  
549 existing condition. An abnormal laboratory finding that requires an action or intervention by  
550 the investigator, or a finding judged by the investigator to represent a change beyond the  
551 range of normal physiologic fluctuation, should be reported as an AE.

552 Adverse events may be treatment emergent (i.e., occurring after initial receipt of  
553 investigational product) or nontreatment emergent. A nontreatment-emergent AE is any new

554 sign or symptom, disease, or other untoward medical event that begins after written informed  
555 consent has been obtained but before the patient has received investigational product.

556 Elective treatment or surgery or preplanned treatment or surgery (that was scheduled prior to  
557 the patient being enrolled into the study) for a documented pre-existing condition, that did not  
558 worsen from baseline, is not considered an AE (serious or nonserious). An untoward medical  
559 event occurring during the prescheduled elective procedure or routinely scheduled treatment  
560 should be recorded as an AE or SAE.

561 The term AE is used to include both serious and non-serious AEs.

### 562 **6.8.2 Serious Adverse Events (SAE)**

563 A serious adverse event is an AE occurring during any study phase (i.e., screening, run-in,  
564 treatment, wash-out, follow-up), at any dose of the study drugs that fulfils one or more of the  
565 following criteria:

- 566 • Results in death
- 567 • Is immediately life-threatening
- 568 • Requires in-patient hospitalization or prolongation of existing hospitalization
- 569 • Results in persistent or significant disability or incapacity
- 570 • Is a congenital abnormality or birth defect in offspring of the patient
- 571 • Is an important medical event that may jeopardize the patient or may require  
572 medical intervention to prevent one of the outcomes listed above.
- 573 - Medical or scientific judgment should be exercised in deciding whether  
574 expedited reporting is appropriate in this situation. Examples of  
575 medically important events are intensive treatment in an emergency  
576 room or at home for allergic bronchospasm, blood dyscrasias, or  
577 convulsions that do not result in hospitalizations; or development of  
578 drug dependency or drug abuse.

579 The causality of SAEs (their relationship to all study treatment/procedures) will be assessed  
580 by the investigator(s) and communicated to local Institutional Review Board.

### 581 **6.8.3 Pregnancy Reports**

582 If a patient becomes pregnant before or during SBRT, the planned or ongoing SBRT should  
583 be discontinued immediately.

584 Male patients should refrain from fathering a child or donating sperm during the study and  
585 for at least 180 days after SBRT. They should also seek the medical advice from the  
586 Investigators in advance before they plan to father a child.

Pregnancy of the patient's partner is not considered to be an AE. However, the outcome of all pregnancies (spontaneous miscarriage, elective termination, ectopic pregnancy, normal birth, or congenital abnormality), if possible, be followed up and documented.

Where a report of pregnancy is received, prior to obtaining information about the pregnancy, the Investigator must obtain the consent of the patient's partner. Therefore, the local study team should adopt the generic ICF template in line with local procedures and submit it to the relevant Institutional Review Boards (IRBs)/Ethics Committee (EC) prior to use.

#### **6.8.4 Assessment of Causality of Adverse Events**

Investigator(s) should use their knowledge of the patient, the circumstances surrounding the event, and an evaluation of any potential alternative causes to determine whether an adverse event is considered to be related to the study treatment, indicating "Yes" or "No" accordingly. The following guidance should be taken into consideration:

- Temporal relationship of event onset to SBRT or LT
- Known association of the event with the disease under study
- Presence of risk factors in the patient or use of concomitant medications known to increase the occurrence of the event
- Presence of non-treatment-related factors that are known to be associated with the occurrence of the event

#### **6.8.5 Methods of Recording Adverse Events**

AEs and SAEs will be collected from the time of the patient signing the informed consent form until the follow-up period is completed. If an event that starts post the defined safety follow up period noted above is considered to be due to a late onset toxicity to study drug then it should be reported as an AE or SAE as applicable.

During the course of the study, all AEs and SAEs should be proactively followed up for each patient for as long as the event is ongoing. Every effort should be made to obtain a resolution for all events, even if the events continue after the patient has discontinued study drug or the study has completed.

Any AEs that are unresolved at the patient's last visit in the study are followed up by the Investigator for as long as medically indicated.

The following variables will be collected for each AE:

In addition, the following variables will be collected for SAEs as applicable:

- AE (verbatim)
- The date when the AE started and stopped
- The maximum CTCAE grade reported
- Changes in CTCAE grade
- Whether the AE is serious or not
- Investigator causality rating against the treatment or procedure(s) (yes or no)

- 624 • Action taken with regard to treatment
- 625 • Administration of treatment for the AE
- 626 • Outcome

627 In addition, the following variables will be collected for SAEs:

- 628 • Date the AE met criteria for SAE
- 629 • Date the Investigator became aware of the SAE
- 630 • Seriousness criteria fulfilled
- 631 • Date of hospitalization
- 632 • Date of discharge
- 633 • Probable cause of death
- 634 • Date of death
- 635 • Whether an autopsy was performed
- 636 • Causality assessment in relation to study treatment or procedure(s)
- 637 • Causality assessment in relation to other medication
- 638 • Description of the SAE

639 The grading scales found in the NCI CTCAE version 4.0 will be utilized for all events with  
640 an assigned CTCAE grading. For those events without assigned CTCAE grades, the  
641 recommendation in the CTCAE criteria that converts mild, moderate, and severe events into  
642 CTCAE grades should be used. A copy of the CTCAE version 4.0 can be downloaded from  
643 the Cancer Therapy Evaluation Program website (<http://ctep.cancer.gov>).

644 Events, which are unequivocally due to disease progression, should not be reported as an AE  
645 during the study.

646 Adverse events and serious adverse events will be recorded from time of signature of  
647 informed consent, throughout the treatment period and including the follow-up period.

648 During the course of the study all AEs and SAEs should be proactively followed up for each  
649 patient. Every effort should be made to obtain a resolution for all events, even if the events  
650 continue after discontinuation/study completion.

651 If a patient discontinues from treatment for reasons other than disease progression, and  
652 therefore continues to have tumor assessments, drug or procedure-related SAEs must be  
653 captured until the patient is considered to have confirmed PD and will have no further tumor  
654 assessments.

655 The investigator is responsible for following all SAEs until resolution, until the patient  
656 returns to baseline status, or until the condition has stabilized with the expectation that it will  
657 remain chronic, even if this extends beyond study participation.

